**DIMER: Deficiency of Immunoglobulin A (IgA) and Microbiome in Respiratory tract infections**

**PID: Primary Immune Deficiency**

### **Medical ethical approval**

The PID study, of which the DIMER-Mycoplasma study is a sub-study, received ethical approval from the Medical Ethical Committee of the Erasmus MC (METC: NL40331.078). All (legal guardians of) subjects signed informed consent and the study was carried out in accordance with the Declaration of Helsinki.

### **Brief description of DIMER-Mycoplasma sub-study**

The DIMER study is a cohort study including children between six weeks and eight years with recurrent respiratory tract infections (rRTIs) and their family members. One of the primary aims is to compare the prevalence of primary antibody deficiencies and *Mycoplasma pneumoniae* carriage in children with rRTIs to controls without infections. In addition, we aim to investigate the mucosal immune system, including differences in mucosal antibody levels and the nasopharyngeal microbiota composition, in children with rRTIs with and without *M. pneumoniae* carriage.

### **Detailed description of DIMER-Mycoplasma sub-study**

#### **Background**

rRTIs frequently affect children (1, 2), with around one-third of children with rRTIs also suffering from recurrent lower RTIs. This can be particularly devastating for young children, as alveoli develop up to the age of seven years (3). As a result of rRTIs at a young age, children may experience lung function loss and chronic obstructive pulmonary disease (COPD) later in life (4-6). Following the introduction of pneumococcal conjugate vaccines, *Mycoplasma pneumoniae* has emerged as the most prevalent bacterial cause of community-acquired pneumonia in hospitalized children in Western countries (7, 8). Like other respiratory pathogens, *M. pneumoniae* pneumonia can be preceded by asymptomatic *M. pneumoniae* carriage in the upper respiratory tract (9, 10). The carriage of potential pathogens is influenced by various factors, including the local respiratory microbiota (11). Furthermore, antibody responses are known to be important for immune protection against *M. pneumoniae* (12).

#### **Objectives**

1. To provide an overview of the prevalence of *M. pneumoniae* carriage in young children with rRTIs and compare this to their family members without infections.
2. To investigate mucosal and systemic immune factors, including (specific) mucosal antibody levels and the local respiratory microbiota, in relation to *M. pneumoniae* carriage in young children with rRTIs.

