#### ***Controls:***

##### *Inclusion criteria:*

Family members of children with rRTIs included in the DIMER study, living in the same household (for most of the time). A family member does not need to be a biological family member if they live in the same household as the patient with rRTIs. Multiple controls can be included per child with rRTIs.

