##### *Exclusion criteria:*

- 1) Known immunodeficiencies (except IgA deficiency),
- 2) Recurrent respiratory tract infections,
- 3) Secondary immunodeficiencies,
- 4) Major congenital anomalies,
- 5) Antibiotic use (prophylactic or course) four weeks prior to inclusion (if this is the only exclusion criteria, a family member can be included but a mucosal sample should be collected four weeks after the last antibiotic course or prophylactic treatment).

Furthermore, subjects with azithromycin prophylaxis three months prior to sampling are also excluded, since this could influence *M. pneumoniae* carriage,

- 6) In the case of a sibling below the age of 16 years: both parents below the age of 18 years,
- 7) Language barrier that prevents a proper informed consent procedure,
- 8) No informed consent.

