#### Clinical data

At inclusion, (caretakers of) subjects will be asked to fill in a questionnaire on their medical history, underlying conditions, and medication use. Furthermore, a longer questionnaire on all medical history, allergies, and asthma will be sent to all caretakers of children with rRTIs. At inclusion, length and weight will be measured and a physical examination will take place. Lab results from the immunological screening will be extracted from the electronic medical file. RTI symptoms at the time of sampling will be registered.

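### The stated comparator is family members without infections, but controls are screened only for recurrent infections, and symptoms at sampling have no stated role in the carriage comparison

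*Protocol*

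**What the plan says.** **Comparator.** Objective 1 (Protocol, Objectives) sets out to measure carriage in young children with rRTIs and "compare this to their family members without infections". The Brief description of the sub-study says the same when it lists the primary aims: "carriage in children with rRTIs to controls without infections".

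**Who can be a control.** The control inclusion criterion is membership of the household: "Family members of children with rRTIs included in the DIMER study, living in the same household (for most of the time"). Among the control exclusions, the only one on infection history is "2) Recurrent respiratory tract infections". Current infection is not mentioned.

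**When the swab is taken.** Under the workflow and Timing of sampling sections, the mucosal sample waits until four weeks have passed without antibiotics. Azithromycin prophylaxis in the three months before sampling is an exclusion. No section makes the swab conditional on absence of symptoms, in cases or controls.

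**Outcome.** Sampling procedures and analyses names qPCR on the nasopharyngeal swab as the means of detecting *M. pneumoniae*. Statistical analyses then refers to carrier status, which is not defined.

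**Symptoms.** Clinical data states that "RTI symptoms at the time of sampling will be registered". The section on infection symptoms grades them in five categories, from none to hospital admission for an RTI. Statistical analyses names age as a possible confounder and plans logistic regression with model choice by AIC. It does not mention the symptom category.

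**The concern.** The objective names one comparison group and the eligibility criteria recruit another. Followed as written, the protocol enrols household members without *recurrent* infections, some of whom may have an infection on the day of the swab.

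The index children are selected for frequent RTIs, so it is reasonable to expect more of them than of their relatives to have symptoms when swabbed. If *M. pneumoniae* is found more often during symptoms, the two groups can differ in qPCR-positive prevalence even when symptom-free carriage is identical. A reader would then take a difference in current infection for a difference in carriage. What is at stake is the interpretation of Objective 1: whether a higher prevalence in children with rRTIs says something about colonisation between infections, or only that they were swabbed during infections more often.

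**Working it through.** **1. Stated comparator against eligible controls.** The protocol gives no figure on this point, so the first check is textual.

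| Question | Objectives and Brief description | Control criteria and sampling rules |
|---|---|---|
| Control with recurrent RTIs | Not in the comparator | Excluded |
| Control with a current RTI, antibiotics in the last four weeks | Not in the comparator | Eligible, swab postponed |
| Control with a current RTI, no antibiotics | Not in the comparator | Eligible, swabbed at inclusion |

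The third row is the contradiction. The second row shows that the antibiotic rule removes part of the treated infections and leaves the untreated ones. In the protocol's symptom grading, these include mild RTI and moderate RTI without antibiotics. The index children have the same sampling rule, so their swabs may also be taken during an untreated RTI.

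**2. How far this could move the comparison.** The protocol gives no detection rates or symptom frequencies. All inputs below are assumptions.

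Let *a* be the detection probability without symptoms and *b* the probability with symptoms, both the same in cases and controls. Let *s* be the share with symptoms at sampling.

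- Prevalence in a group: p = a(1 − s) + b·s
- Odds ratio: OR = [p₁/(1 − p₁)] / [p₀/(1 − p₀)], with cases 1 and controls 0

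| a | b | s cases | s controls | p cases | p controls | OR |
|---|---|---|---|---|---|---|
| 10% | 10% | 60% | 20% | 10% | 10% | 1.00 |
| 10% | 20% | 50% | 20% | 15% | 12% | 1.29 |
| 10% | 30% | 60% | 20% | 22% | 14% | 1.73 |
| 5% | 25% | 60% | 20% | 17% | 9% | 2.07 |

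Third row in full: cases 0.10 × 0.40 + 0.30 × 0.60 = 0.22; controls 0.10 × 0.80 + 0.30 × 0.20 = 0.14; OR = (0.22/0.78) / (0.14/0.86) = 0.282/0.163 = 1.73.

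Fourth row: cases 0.05 × 0.40 + 0.25 × 0.60 = 0.17; controls 0.05 × 0.80 + 0.25 × 0.20 = 0.09; OR = (0.17/0.83) / (0.09/0.91) = 0.205/0.099 = 2.07.

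In every row the OR within each symptom stratum is 1 by construction. Anything above 1.0 in the last column comes only from the different symptom mix. The OR is also 1.0 whenever *s* is the same in both groups, whatever *a* and *b* are.

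**The case against.** **The wording is shorthand.** The Brief description sets children with rRTIs against "controls without infections", so infections may simply mean the recurrent ones just named. That is probably the intention. The text does not say it, though, and the unqualified phrase stands in two places that define the aim. If it is shorthand, correcting it costs nothing.

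**Every positive qPCR is counted as carriage.** A reader might infer this, because qPCR is the only detection method named. The protocol does not state it; carrier status is left undefined. What can be said is that no rule prevents a positive result during an RTI from being counted.

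**Carriage means symptom-free carriage.** A reader might also infer this from the Background, which speaks of asymptomatic "carriage in the upper respiratory tract" before pneumonia. That sentence describes one sequence of events and does not define the term. One of the references cited for it is, by its title, an observational study of carriage in symptomatic and asymptomatic children. An all-swab prevalence is therefore a legitimate reading of Objective 1.

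**The role of symptoms may be left to the SAP.** Choice of covariates and strata often is, and the SAP is not at hand. The planned multivariable model could take the symptom category. This stands as far as the modelling goes. It does not remove the mismatch between objective and control criteria, which are both protocol content.

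**The size is assumed.** This stands. The three inflated rows need detection to rise two- to five-fold with symptoms, and the listed symptoms are non-specific. Nothing in the protocol supports a particular ratio, so the no-effect case belongs in the range.

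**A symptom-free primary analysis would be worse.** This stands too. It changes the question from prevalence in children with rRTIs to prevalence in those well on the day. A single symptom such as rhinitis would drop a child from the set, and selection would rest on something that may itself be a consequence of *M. pneumoniae*.

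**Conclusion.** The point holds in a limited form. The objective and the control criteria disagree about who the controls are. People with a current untreated RTI can be swabbed in both groups, and the symptom category recorded at sampling is not linked to the comparison. A difference in qPCR-positive prevalence may therefore partly reflect more frequent current RTI among the index children.

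The protocol does not allow the size or even the direction of this effect to be derived. With equal symptom-free carriage, the assumed inputs give an OR from 1.0 to about 2.1. The upper part of that range requires both that symptoms raise detection and that the index children have symptoms more often. A stronger conclusion, that the planned comparison is biased or that the outcome is mislabelled, is not supported.

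**What to change.** 1. In Objectives and in the Brief description, change the comparator to family members or controls *without recurrent respiratory tract infections*, so that it matches the control criteria.
2. Keep the all-swab comparison as the main analysis of Objective 1.
3. Add to Statistical analyses a prespecified comparison of qPCR-positive prevalence by symptom category at sampling in both groups, with a sensitivity analysis restricted to category 1 (no symptoms). Any claim about asymptomatic carriage should rest on that subset. If the SAP already contains this, a cross-reference is enough.
4. Confirm that symptoms at sampling are recorded for family members as well as index children. Clinical data does not limit the recording to one group, but does not spell this out either.

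If step 4 is confirmed, no new data are needed. The cost is a little more analysis and wide intervals in small strata; sparse categories may have to be combined, by a rule fixed in advance.

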## **Study subjects**

### **In- and exclusion criteria**

#### ***Children with recurrent respiratory tract infections:***

##### *Inclusion criteria:*

Children aged six weeks to eight years (until the day they turn eight years old) who are referred to a participating hospital for rRTIs with an indication for immunological screening. rRTIs are defined according to the guideline of the Dutch Section of Pediatric Infectious Diseases & Immunology, and as described by Gruber et al. (13, 14). The choice for immunological screening is based on the physician's professional opinion after the clinical consultation and physical examination. Furthermore, children with an already known IgA deficiency (2SD below age-appropriate reference values (see appendix 1)) diagnosed within the year before inclusion, are also included.

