##### *Exclusion criteria:*

- 1) Primary immunodeficiency for which intravenous immunoglobulin (IVIG) treatment has started,
- 2) Secondary immunodeficiencies (e.g. HIV, chemotherapy, transplantation),
- 3) Major congenital anomalies (eponymous syndromes, chromosomal abnormalities, cleft palate, renal or hepatic insufficiency, known glucose-6-phosphate deficiency, cystic fibrosis, primary ciliary dyskinesia or acute porphyria),
- 4) Antibiotic use (prophylactic or course) four weeks prior to inclusion (if this is the only exclusion criteria, a child can be included but a mucosal sample should be collected four weeks after the last antibiotic course or prophylactic treatment). Furthermore, subjects with azithromycin prophylaxis three months prior to sampling are also excluded, since this could influence *M. pneumoniae* carriage,
- 5) Both parents below the age of 18 years,
- 6) Language barrier that prevents a proper informed consent procedure,
- 7) No informed consent.

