14. Driessen GJA. Evidence-based richtlijn diagnostiek naar onderliggende aandoeningen bij kinderen met recidiverende luchtweginfecties: Erasmus MC, Sophia Kinderziekenhuis, subafdeling kinderinfectziekten-immunologie; 2016 [Available from: <https://www.kinderinfectziekten.nl/wp-content/uploads/2016/09/12-07-2016-Diagnostiek-recidiverende-luchtweginfecties.pdf>].

## Appendix 1

**Definition of antibody deficiencies:** An IgA, IgG (subclass) or IgM deficiency was defined as having an IgA or IgG (subclass) level below minus two standard deviation (-2SD) of age-specific reference values.

The following reference values, as used in Dutch clinical practice, were applied:

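### Known IgA deficiency is itself a route into the case group, which biases the comparison of IgA-deficiency prevalence upward in cases; the rules for other known deficiencies also differ between groups

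*Protocol*

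**What the plan says.** - **Aim.** The brief description of the sub-study says: "One of the primary aims is to compare the prevalence of primary antibody deficiencies", together with *M. pneumoniae* carriage, in children with rRTIs and in controls. The two numbered items under Objectives cover carriage prevalence and immune factors related to carriage. They do not repeat the deficiency comparison.
- **Ordinary route for cases.** Children "who are referred to a participating hospital for rRTIs with an indication for immunological screening". The physician decides whom to screen after seeing the child.
- **Extra route for cases.** The same paragraph adds that "children with an already known IgA deficiency (2SD below age-appropriate reference values (see appendix 1)) diagnosed within the year before inclusion, are also included".
- **Outcome definition.** Appendix 1 defines a deficiency as a "level below minus two standard deviation (-2SD) of age-specific reference values". The extra route uses the same limit.
- **Exclusions.** Cases are excluded for "Primary immunodeficiency for which intravenous immunoglobulin (IVIG) treatment has started". Controls are excluded for "Known immunodeficiencies (except IgA deficiency"), whether treated or not.
- **Analysis.** The Statistical analyses section names age as the possible confounder and does not mention entry route.

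**The concern.** A prevalence comparison needs each group to be assembled without regard to the outcome, or at least by the same rule. Here a child found IgA-deficient in the past year can be enrolled because of that result. A child screened in the same year with a normal result has no corresponding way in. The one-year look-back therefore collects positives only.

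A second asymmetry concerns the other antibody deficiencies. A family member with a known, untreated IgG, IgG-subclass or IgM deficiency is removed, while a child with rRTIs and the same finding stays. At stake is a reported case-control difference in deficiency prevalence produced partly by enrolment.

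**Working it through.** The Protocol states no sample size, prevalence or expected difference, so there is no figure of its own to reproduce. All rates below are assumptions. Both parts start from equal true prevalence in the two groups (true odds ratio 1).

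**A. IgA deficiency**

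Let p be the true prevalence in both groups and f the share of enrolled cases who enter solely through the known-IgA route. Each such child is taken to count as deficient. Known IgA deficiency does not exclude a control, so controls show p.

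- Observed prevalence in cases = f + (1 − f)p.
- Spurious odds ratio = observed odds in cases ÷ odds at p, which simplifies to 1 + f / [(1 − f)p].

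| p | f | Cases observed | Controls | Spurious OR |
|---|---|---|---|---|
| 8% | 10% | 0.10 + 0.90 × 0.08 = 17.2% | 8% | 1 + 0.10/0.072 = 2.4 |
| 15% | 5% | 0.05 + 0.95 × 0.15 = 19.25% | 15% | 1 + 0.05/0.1425 = 1.35 |
| 5% | 20% | 0.20 + 0.80 × 0.05 = 24% | 5% | 1 + 0.20/0.04 = 6.0 |
| 5% | 10% | 0.10 + 0.90 × 0.05 = 14.5% | 5% | 1 + 0.10/0.045 = 3.22 |

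The second and third rows are the extremes for p of 5–15% and f of 5–20%. In the last row, with an assumed 100 per group and a two-sided 5% test, a difference would be declared about 62% of the time although none exists.

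With f = 0 the spurious odds ratio is 1.00.

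**B. Other antibody deficiencies**

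Let q be the true prevalence in both groups, k the share already known before enrolment (taken as equal in both groups), and t the share of known cases in whom IVIG has started.

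- Controls: all known deficiencies are removed, so prevalence = q(1 − k)/(1 − qk).
- Cases: only the IVIG-treated are removed, so prevalence = q(1 − kt)/(1 − qkt).
- Spurious odds ratio = (1 − kt)/(1 − k), whatever q is.

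| k | t = 0 | t = 0.5 | t = 1 |
|---|---|---|---|
| 25% | 1/0.75 = 1.33 | 0.875/0.75 = 1.17 | 1.00 |
| 50% | 1/0.50 = 2.00 | 0.75/0.50 = 1.50 | 1.00 |

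Example: q = 5%, k = 50%, t = 0 gives 5.0% in cases and 0.025/0.975 = 2.56% in controls.

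With equal k the ratio stays above 1 unless every known case is on IVIG. If deficiencies are more often already known in cases than in controls, the ratio becomes (1 − k_case × t)/(1 − k_control). That falls below 1 when k_case × t exceeds k_control.

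**C. Could the IVIG exclusion cancel the IgA route in a pooled prevalence?**

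Suppose the IVIG exclusion removes a share v of the rRTI population, all of them deficient. Setting f + (1 − f)(p − v)/(1 − v) = p gives v = f. At p = 10% and f = 5%, half of all deficient children would have to be on IVIG and excluded for the two effects to cancel. This part leaves out the controls' exclusion in B.

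**The case against.** Several counter-arguments have weight.

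- **The aim belongs to the wider study.** The deficiency comparison is worded as an aim of DIMER, and the numbered objectives concern carriage only. This stands and limits the reach of the point: carriage prevalence is affected only if deficiency itself alters carriage. It does not remove the point, because the sub-study description still names the comparison as a primary aim.
- **Not every known-IgA child is surplus.** Some will also have been referred for rRTIs with a screening indication. The formula holds only for those who enter solely by the extra route, so applying it to all of them would overstate the bias. A diagnosis up to a year old may also not be confirmed on repeat measurement, and the Protocol does not say which value counts.
- **The IVIG exclusion pulls the other way.** It lowers deficiency among cases. A reader might infer that the entry rules simply inflate every deficiency in cases and deflate every deficiency in controls. The document does not support that: controls with known IgA deficiency are kept, and the net effect on a pooled prevalence depends on unstated rates.
- **Objective 2.** A reader might infer that enrolling more children with low IgA also biases the relation between IgA and carriage. Low IgA is the exposure there. Over-sampling on exposure does not by itself bias an exposure-carriage odds ratio, and nothing in the Protocol suggests that selection by this route also depends on carriage.
- **Analysis sets may be left to a statistical analysis plan.** That is fair, and silence on entry route in the Statistical analyses section is weak evidence. The entry rules, however, are fixed in the Protocol.

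**Conclusion.** The point holds in limited form. For IgA deficiency, the extra entry route biases case prevalence upward, and the direction is clear provided some children enter solely by it and are counted as deficient. Its size cannot be read from the Protocol. Under assumed true prevalences of 5–15% and route shares of 5–20%, the spurious odds ratio runs from 1.35 to 6.0, with 2.4 at 8% and 10%.

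For other deficiencies the two groups face different exclusions and are not comparable. With equal true prevalence and an equal share already known, this favours a higher rate in cases unless all known cases are on IVIG. The net effect on any-deficiency prevalence is undetermined.

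The point bears on the deficiency-prevalence aim. It does not show that the carriage objectives are invalid, so it is a correction to one comparison and not a fundamental defect of the sub-study.

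**What to change.** 1. Record the entry route of every case: referral with a screening indication, known IgA deficiency, or both.
2. Leave children who qualify solely by known IgA deficiency out of the numerator and denominator of the deficiency-prevalence comparison, and report them separately. Children who also qualify by referral stay in; removing them would push case prevalence too low.
3. For that comparison only, apply to cases the same exclusion for known non-IgA deficiency as to controls. The result should then be described as the prevalence of previously unrecognised non-IgA deficiency.
4. Keep the known-IgA-route children in the Objective 2 analyses. At most, repeat the Objective 1 carriage comparison without them as a sensitivity check.

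Adding screened-out controls back into the count is not recommended, because the Protocol describes no log or data for family members who fail the criteria.

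The cost is one flag, taken from inclusion records, and a small loss of cases in one analysis.

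### The IgA-deficiency entry route does not state that recurrent infections are required, so, as worded, the group analysed as children with rRTIs can include children without them

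*Protocol*

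**What the plan says.** All references are to the Protocol.

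- **Case group, Inclusion criteria.** Under the heading "Children with recurrent respiratory tract infections", the first route takes children aged six weeks to under eight years "who are referred to a participating hospital for rRTIs with an indication for immunological screening". A second sentence then adds that "children with an already known IgA deficiency (2SD below age-appropriate reference values (see appendix 1)) diagnosed within the year before inclusion, are also included". Its closing words, "diagnosed within the year before inclusion, are also included", make this, as worded, an additional way in.
- **Case group, Exclusion criteria.** There are seven items. The only one on primary immunodeficiency concerns patients already started on intravenous immunoglobulin. None concerns a child who does not have rRTIs.
- **Controls, Inclusion criteria.** Controls are "Family members of children with rRTIs included in the DIMER study, living in the same household (for most of the time").
- **Controls, Exclusion criteria.** Having rRTIs excludes a control. So does the item "Known immunodeficiencies (except IgA deficiency"), which leaves IgA-deficient household members eligible.
- **Population as described elsewhere.** The brief description of the sub-study speaks of "children between six weeks and eight years with recurrent respiratory tract infections (rRTIs) and their family members". Objective 1 is to estimate carriage "in young children with rRTIs and compare this to their family members without infections".

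**The concern.** Having or not having rRTIs is the contrast in objective 1. The group labelled as having them should therefore contain only children who do, and the criterion that decides entry should say so. The second route does not. Centres could reasonably apply it in different ways, and a child admitted on IgA deficiency alone would be analysed under a label that does not fit.

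Three analyses would be affected:

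- the carriage comparison in objective 1;
- the comparison of antibody-deficiency prevalence between children with rRTIs and controls, which the brief description names among the primary aims;
- objective 2, which relates mucosal and systemic immune factors to carriage within children with rRTIs.

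In the last two, the extra children would have been selected on a quantity under study.

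**Working it through.** **Step 1. Apply the criteria to three hypothetical children.** Each has an IgA deficiency established in the preceding year, no rRTIs, and no other reason for exclusion.

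- *Child A: under eight, no household link to an included child.* The first case route fails, since there was no referral for rRTIs. The second is met as worded, and no case exclusion applies. The control criteria fail for want of a shared household. Result: a case on the literal reading, and never a control.
- *Child B: as A, but living with an included child with rRTIs.* The second case route is met as worded. The control inclusion is also met. The control exclusion for rRTIs does not apply, and IgA deficiency is exempted. Result: eligible for both groups, with no explicit rule to choose between them.
- *Child C: past the eighth birthday.* The age limit stands only in the sentence on the first route, so the second admits this child as worded, although the brief description gives the age limit for the whole cohort.

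If the case-group heading is instead treated as a binding requirement, all three fail the case criteria. The result turns on whether a heading supplies a condition that the criterion omits.

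**Step 2. Objective 1.** The Protocol gives no sample size, carriage rate or number entering by the second route, so there is no figure of its own to reproduce. The effect can be written only in symbols. Let p1 be carriage in children with rRTIs, p0 carriage in controls, p2 carriage in children admitted on IgA deficiency without rRTIs, and f their share of the case group.

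Observed difference = (1 − f)·p1 + f·p2 − p0 = (p1 − p0) − f·(p1 − p2).

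- If p2 = p0, this becomes (1 − f)·(p1 − p0). For assumed f of 5%, 10% and 20%, the comparison keeps 95%, 90% and 80% of the true difference.
- If p2 lies above p1, the observed difference is larger than the true one. The Background section says that antibody responses matter for protection against *M. pneumoniae*, so p2 = p0 cannot be taken for granted.

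**Step 3. Antibody-deficiency prevalence.** Let q be the prevalence among cases who do have rRTIs. Every child added by the second route is deficient by the Appendix 1 definition, so

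Observed prevalence = (1 − f)·q + f = q + f·(1 − q).

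This always exceeds q when q is below 1. The rise is at most f, that is, at most 5, 10 or 20 percentage points for the same assumed values.

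**Step 4. Objective 2.** Serum IgA is among the measurements in the sampling section, and objective 2 covers systemic immune factors. Children admitted because of low IgA and without rRTIs lie outside the stated population and are selected on one of the factors examined. The Protocol allows no size to be put on this.

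**The case against.** The strongest reply is that rRTIs were always meant to be required. The heading covers both sentences. The brief description, both objectives and the control criteria treat every index child as having rRTIs. The second sentence follows directly on the one about the physician's choice of immunological screening, so it may only waive a new screening indication for children with rRTIs whose deficiency is already known. Family members are approached as controls after the index child is included, so in practice a sibling without rRTIs would probably become a control.

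This is a plausible account of the intention, and it stands as such. It does not remove the ambiguity, because the operative sentence adds children without stating the condition and nothing in the exclusions supplies it. If the narrow reading was intended, the correction merely writes it down.

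Three stronger inferences are not supported:

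- *That every such child meets both sets of criteria.* Control status also requires a shared household with an included child with rRTIs, so Child A can never be a control.
- *That the study creates dually eligible children by finding low IgA in a control's serum.* The deficiency must already be known before inclusion, and consent comes before sampling. A deficiency first found in study serum does not satisfy the second route.
- *That the heading is the only sign that rRTIs are required.* The brief description, the objectives and the control criteria point the same way.

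**Conclusion.** The wording defect is real and is worth correcting. Applied literally, the second route admits children without rRTIs, and without a stated age limit, to a group that the rest of the Protocol describes as children with rRTIs. For a household child under eight it also leaves the group open.

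The size of the problem cannot be derived. The fraction f is not given, and nothing in the Protocol shows that any such child has been enrolled. A reader might infer a definite dilution of the carriage difference. That holds only if these children carry at the control rate; otherwise neither size nor direction is known. The upward effect on antibody-deficiency prevalence among cases is certain in direction for any f above zero (with q below 1), but it too depends on f. The point is an unresolved contradiction between the entry criterion and the stated population, and not a demonstrated bias.

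**What to change.** 1. Make the IgA-deficiency route conditional: the child must also meet the rRTI definition and the same age limit as the first route.
2. State that a household member without rRTIs belongs to the control group whatever the IgA status.
3. Record for each case the route of entry and whether the rRTI definition was met.
4. If any child has been included on IgA deficiency without rRTIs, leave that child out of the rRTI group in the objective 1 and 2 analyses and in the antibody-deficiency comparison. Describe these children separately and report their number, which gives f.

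The cost is a sentence or two of text and a data flag. The downside is the possible loss of a few children from the case group. If the narrow reading was applied throughout, nobody is lost.
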